**Cost items for diagnosis for the relative if accompanied**

1. number of travel days _____ travel expense per day ___travel hours__
2. number of hours spent in the health institution per day ____________
3. expenses for food ______ drink _________ others with expense _____

**Cost items for treatment and follow up of the patient**

1. number of travel days _____ travel expense per day ___travel hours__
2. number of hours spent in the health institution per day ____________
3. expenses for food _______ drink ________ others with expense _____

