**Study - III**

This is a randomized controlled community trial to find out the cost per tuberculosis patient treated successfully. The study follows societal perspective of cost analysis. The main cost items related to the costs of tuberculosis prevention and control programme will be collected as for diagnosis, follow up and supervision including patient and community health workers time and costs. Data collectors will also get records from district finance offices. The data collectors will calculate cost of time based on monthly salary of health workers and tuberculosis patients if they are in the productive age groups. In addition, the cost of the person accompanying the patient will be included. The outcome indicator for the study is the cost per patient treated successfully.

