**2. Methods**

**2.1. Study design**

This is a randomized controlled community trial to find out the costs per tuberculosis patient treated successfully in the intervention and non-intervention districts. Cost related to tuberculosis control programme in the study sites will be determined according to the actual expenses and time cost. Programme coordinators, health workers, community health agents, tuberculosis treatment supervisors, tuberculosis patients and relatives accompanying them to health facilities in the study sites will be included in the study.

The cost analysis will follow societal perspective to analyse the cost per patient. The data collectors will obtain financial reports from districts and health institutions finance sections to collect expenditures for tuberculosis control programme, health workers and community health agents’ time and costs associated to tuberculosis prevention and control activities. In addition, they will collect cost of the patient and the relative who accompanied them during their visit to health institutions.

The investigator will use cost per tuberculosis patient successfully treated as an outcome measure. Future cost and productivity gains will not be included in the study. Standard cost estimation of all expenses and time of the patient, treatment supervisor and health workers will be done. Data collectors will use a structured pre-tested questionnaire for data collection.

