**Cost items for diagnosis for the patient**

1. number of travel days ____ travel expense per day ____travel hours__
2. expenses for food ________ drink _______ others with expense _____

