**Cost items for treatment supervision**

1. number of hours spent per for treatment supervision ______________
2. total number of days tuberculosis patient is supervised ____________
3. number of travel hours for drug collection _______________________
4. number of days traveled for drug collection ______________________
5. travel expenses per day _____________________________________
6. related expenses for food ___________ drink __________ others ___

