**COMMUNITY BASED TUBERCULOSIS CARE – DISTRICT FORM**

**Questionnaire no.________ Name of interviewer __________ Date___________**

**Resources for tuberculosis control**

1. Health manpower for tuberculosis control

Profession____________________ monthly salary________ __________

2. Motor bike________________ number ___________

3. Budget allocated for tuberculosis control programme _________________

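### The Study III patient form omits relatives' costs during treatment, the patient's facility hours at diagnosis, and patient income, all of which the stated societal costing needs

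*Protocol*

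**What the plan says.** The protocol describes the costing twice. Study Three, section 2.1, sets the perspective: "The cost analysis will follow societal perspective to analyse the cost per patient". It continues: "In addition, they will collect cost of the patient and the relative who accompanied them during their visit to health institutions". The same section undertakes to estimate the time and expenses of patients, treatment supervisors and health workers, and names cost per successfully treated patient as the outcome. Section 2.2 extends the costing over case detection, treatment and follow-up. Section 6.2, Study III, gives the valuation rule, under which data collectors will "calculate cost of time based on monthly salary of health workers and tuberculosis patients if they are in the productive age groups", and says that the accompanying person's cost is to be counted. None of these statements limits relatives' costs to the diagnostic phase.

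The annexed TB patient form has a socio-demographic block and three cost blocks. The first cost block is headed "Cost items for diagnosis for the patient", the second covers an accompanying relative at diagnosis, and the third is headed "Cost items for treatment and follow up of the patient". The laboratory technician form comes next.

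**The concern.** A cost that is promised in the methods but not asked on the form will not be in the data. Relatives' visits and patients' waiting hours are household quantities, so no facility ledger or finance report holds them and no later analysis can restore them. They enter the Study III outcome directly, as part of the numerator of cost per patient successfully treated.

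The two arms also differ in where care happens. Control patients follow facility-based case finding and treatment. Intervention patients take treatment in the community under a supervisor, and community health workers collect and carry the sputum. A gap in what is asked about facility visits is therefore unlikely to be equal in the two arms, and the comparison between arms is what the costing is for.

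**Working it through.** **The plan's own figure.** The only computed result in Study Three is the sample size. With p1 = 0.30, p2 = 0.13, P = 0.215 and z values 1.96 and 1.28, the usual formula gives n = (1.96 + 1.28)² × 2 × 0.215 × 0.785 / (0.30 − 0.13)² = 122.6, so 123. The design effect is 1 + (15 − 1) × 0.04 = 1.56, and 1.56 × 123 = 191.9, so 192. Both figures reproduce, and the point made here does not depend on them.

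**Promise against form.**

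| Cost component | Promised in | Asked on the TB patient form |
|---|---|---|
| Patient's travel and expenses, diagnosis | Study Three, 2.1 and 2.2 | Yes |
| Patient's facility hours, diagnosis | Study Three, 2.1 and 2.2 | **No** |
| Relative's travel, facility hours and expenses, diagnosis | Section 6.2; Study Three, 2.1 | Yes |
| Patient's travel, facility hours and expenses, treatment | Study Three, 2.1 and 2.2 | Yes |
| Relative's travel, facility hours and expenses, treatment | Section 6.2; Study Three, 2.1 and 2.2 | **No** |
| Patient's income, to value time | Section 6.2 | **No**; occupation only |

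The facility-hours item appears in two of the three cost blocks and is missing from the patient's own diagnosis block, which looks like an oversight. The laboratory technician, TB OPD and community health worker forms each ask monthly income, so the item was available and was not carried to the patient form.

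**Difference between arms.** Study Two places control patients in facility-based case finding and treatment, and the TB OPD form costs daily dosing there in the intensive phase. Section 6.2, Study II, places intervention patients in community treatment. Relatives' treatment visits and patients' hours at diagnosis should therefore arise mainly in the control arm. This is an inference from the two care pathways; the protocol does not state it.

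**Illustration.** The documents give no accompaniment rate and no visit count. Assume 60 facility visits per control patient (daily visits over two months), 2 to 8 per intervention patient, and a relative present at 10% to 50% of them. Unrecorded relative-visits per patient are then:

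- control: 0.10 × 60 = 6 to 0.50 × 60 = 30;
- intervention: 0.10 × 2 = 0.2 to 0.50 × 8 = 4.

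These are visits, not full days, and they show only the order of the gap under those assumptions.

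**The case against.** Several defences deserve weight.

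- **Income is recoverable.** The form records occupation, so a wage by occupation could be applied after data collection, and such a rule could sit in an analysis plan that is not shown. This stands for valuation: the income gap is a mismatch with the salary rule, not an irrecoverable loss. It does not help with relatives' treatment visits or patients' diagnosis hours, where the quantity itself is not asked.
- **The forms are to be pretested.** Missing items might be caught then. That is possible, but the annexed form is what the plan fixes. The entry for other expenses in the treatment block might pick up some of a companion's cash outlay, though not the companion's time.
- **A line may have been lost in conversion.** Numbering restarts within the patient form, so this cannot be wholly excluded. The blocks read as complete and no gap is marked.

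Three stronger readings are tempting and are not supported.

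- A reader might infer that supervisors' time cannot be valued because their form lacks income. The salary rule names only health workers and patients; supervisors are volunteers, and the block "Cost items for treatment supervision" records their hours, days and expenses. A proxy wage would serve.
- A reader might infer from the district form, with its item "3. Budget allocated for tuberculosis control programme" and no cluster field, that district costs cannot be split between arms. Study Two draws clusters from within districts, but Study Three speaks of intervention and non-intervention districts, so it is not established that arms share one. The form also records visits, hours, kilometres, and facilities and workers supervised, which could serve to apportion costs.
- A reader might infer a signed overall bias. If supervisors' time were left unvalued, intervention cost would be understated, which works against the control-arm gap.

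**Conclusion.** The point holds as an inconsistency between the costing methods and the patient form on three items: relatives' costs during treatment and follow-up, the patient's facility hours at diagnosis, and patient income. The first two would be lost for good if the form were used as annexed. The third leaves the stated salary rule without its input. On the first two items the control arm's cost per patient successfully treated would probably be understated, given that its diagnosis and treatment take place at facilities. The total size of the bias, and its net direction once other gaps are counted, cannot be determined from the document; the 6 to 30 relative-visits per control patient rest wholly on assumed visit counts and accompaniment rates. The comparison of treatment success in Study Two is not affected.

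**What to change.** Before data collection, add to the TB patient form:

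1. a relative block under treatment and follow-up, with travel, facility hours and expenses, matching the block already used at diagnosis;
2. the patient's facility hours at diagnosis;
3. the patient's income.

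In the Study Three methods, state one proxy wage, used in both arms, for patients, relatives and treatment supervisors who have no salary. Relatives need it as well, because no form asks their income and even their recorded diagnosis hours have no value attached. The cost is a few extra questions and slightly longer interviews.

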**COMMUNITY BASED TUBERCULOSIS CARE – LAB TECHNICIAN FORM**

**Questionnaire no.__________ Name of interviewer ___________ Date___________**

**Socio-demographic variables**

1. Name of health worker _________________ 2. Age________3. Sex ____

4. Health facility ______________ profession __________ 5. Religion __

6. Monthly income _______________

7. Marital status Single___ Married___ Divorced___ Widowed____ other___

**Cost items for laboratory sputum microscopy**

1. number of hours taken for explaining about sputum specimen collection __
2. number of hours taken for sputum staining, microscopy and reporting____

**Cost items for laboratory for follow up sputum**

1. number of hours taken for explaining about sputum specimen collection
2. number of hours taken for sputum staining, microscopy and reporting__

**COMMUNITY BASED TUBERCULOSIS CARE – TB OPD FORM**

**Questionnaire no.__________ Name of interviewer ___________ Date___________**

**Socio-demographic variables**

1. Name of health worker __________________ 2. Age________3. Sex __

4. Health facility ____________ profession ___________ 5. Religion __

6. Monthly income _______________

7. Marital status Single___ Married___ Divorced___ Widowed____ other___

**Cost items for daily dose of intensive phase treatment**

1. number of hours taken for explaining about the disease to the patient _
2. number of hours taken for daily dose supervision and registration _____

**Cost items for continuation phase treatment**

1. number of hours taken for explaining about the disease process ______
2. number of hours taken for drug administration and registration _______

**COMMUNITY BASED TUBERCULOSIS CARE – TTS FORM**

**Questionnaire no.________ Name of interviewer __________ Date___________**

**Socio-demographic variables**

1. Name of TTS________________________ 2. Age________3. Sex ______

4. Cluster ________________ Kebele ___________ 5. Religion _______

6. Marital status Single___ Married___ Divorced___ Widowed____ other____

7. Educational status No schooling ____ Grade ____ other ________

8. Occupation of suspect Farmer ___ student ___ merchant ____others __

**Cost items for treatment supervision**

1. number of hours spent per for treatment supervision ______________
2. total number of days tuberculosis patient is supervised ____________
3. number of travel hours for drug collection _______________________
4. number of days traveled for drug collection ______________________
5. travel expenses per day _____________________________________
6. related expenses for food ___________ drink __________ others ___

**COMMUNITY BASED TUBERCULOSIS CARE – CHW FORM**

**Questionnaire no.________ Name of interviewer __________ Date__________**

**Socio-demographic variables**

1. Name of CHW_______________________ 2. Age________3. Sex ______

4. Cluster ________________ Kebele ___________ 5. Religion _______

6. Marital status Single___ Married___ Divorced___ Widowed____ other____

7. Educational status No schooling ____ Grade ____ other ________

8. Occupation of suspect Farmer ___ student ___ merchant ____others __

9. Monthly income __________

**Cost items for sputum collection**

1. number of hours spent per community education _________________
2. total number of days community mobilization conducted____________
3. total number of hours spent for sputum collection ________________
4. total number sputum collected per session ______________________
5. number of hours spent on sputum transportation _________________
6. number of days sputum is transported to health facilities ___________
7. number of hours spent for sputum result collection _______________

**Cost items for treatment**

17. Number of hours spent about sputum result and TTS selection ________

18. Number of hours spent in discussion with TTS _____________________

19. Number of hours spent on drug collection from health facilities ________

20. Number of days traveled for drug collection _______________________

21. Expenses for food ________ travel _________ others _______________

22. Number of hours spent on supervision ___________________________

23. Number of days supervision is conducted _________________________

**COMMUNITY BASED TUBERCULOSIS CARE – DISTRICT FORM**

**Questionnaire no.________ Name of interviewer __________ Date___________**

**Resources for tuberculosis control**

1. Health manpower for tuberculosis control

Profession____________________ monthly salary________ __________

2. Motor bike________________ number ___________

3. Budget allocated for tuberculosis control programme _________________

**Cost items for supervision**

4. Number of supervisory visits conducted __________________________

5. Number of hours spent per supervision __________________________

6. Number of health facilities supervised per supervision ________________

7. Number of community health workers supervised per supervision ______

8. Number of kilometers traveled per supervision _____________________

9. Total expenditure for fuel for supervision of TB programme____________

* other costs will be obtained from the finance report

**Serosurvey among tuberculosis patients in southern region**

Study site ______________ Date ___________

Patient code no _______________ Age __________ Sex __________

Address Urban ___________ Rural _______________

Diseases category a) New b) Relapse c) treatment after default

Disease classification a) smear positive b) smear Negative c) EPTB

Name of responsible health worker ________________

Signature ____________

**Acceptability of community tuberculosis care - TB patients**

Identification

1. Name______________________

2. District_________Cluster ______Kebele`___________

Socio-demographic variables

3. Age _________ 4. Sex: _____

4. Marital status Single __ Married __ Divorced __ Widowed ___Other___

5. Religion Protestant ___ Muslim ___ Orthodox ___ Other ____

6. Educational level No schooling ___ Grade ________

7. Occupation Farmer__Govt employee__Student__Housewife__other___

Acceptability questions

1. Do you accept tuberculosis treatment in the community Yes __ No _

2. If yes, why?

a) Time

b) Cost

c) Travel

d) Environment

e) Type of supervisor

f) Understanding each other

g) Flexible time place

h) Better care and adequate time for discussion

i) Trust each other

j) Decrease stigma and discrimination

k) Could do it with out worrying other members

l) others specify

3. If No, Why?

a) Professional incompetence

b) Poor drug storing

c) Stigma

d) specify

